### Primary Outcome

The primary outcome of interest is PrEP uptake defined as filling the PrEP prescription and taking at least 1 dose of the medication by 2 weeks following their visit with the PrEP provider. The primary outcome will be measured at 12 weeks post completion of the 4-week motivational sessions.

### Secondary Outcome

The secondary outcome of interest is daily PrEP adherence as measured by the proportion of videos uploaded showing medication being taken (intervention group only), the proportion of self-reported daily adherence (intervention and control group), levels of tenofovir (TFV) urine concentrations (>1000 ng/mL) [75] detected in urine measured at 12-weeks post-PrEP initiation (both groups). According to previous research, urine concentrations of TFV at >1000 ng/mL is indicative of use of oral PrEP in the previous 3 days (high adherence), detectable levels of TFV but <1000 ng/mL are indicative of low adherence and undetectable levels of TFV suggesting nonadherence [75]. Studies have also shown that directly observed therapy is useful for interpreting PrEP adherence. This provides an additional layer of certainty regarding this method of measuring this important secondary outcome [76]. Medication adherence for long-acting injectable PrEP will be determined by examining medical records for the timing of the dose.

### Other Outcomes

Other outcomes of interest include intervention feasibility (enrollment rate, session attendance, use of Scene Health, and study retention), and intervention acceptability (client satisfaction scores).

### Safety Considerations

A data safety monitoring board affiliated with the CNRA will provide oversight for this study including the possibility of loss of confidentiality. The Scene Health mobile app is HIPAA-compliant and allows for secure messaging and encrypted videos, Access to the app requires a participant to log in with credentials. Videos submitted to the app are not available in the device gallery and videos are deleted from the device once received by Scene Health’s secure server. Only approved project staff will have access to the participant data via the “Backstage” by Scene Health web portal.

### Statistical Analysis

Generalized linear modeling will model effects of the proportion of participants who fill their prescription and take at least one dose as a function of intervention group. In unique models, generalized linear modeling will evaluate 2 secondary outcomes as a function of intervention group: (1) dichotomous verification of adherence based on urine TFV levels >1000 ng/mL (no vs yes), and (2) TFV levels >1000 ng/mL indicating recent adherence, detectable levels of TFV but <1000 ng/mL indicating low adherence and undetectable levels of TFV suggesting nonadherence [75].

Where necessary, generalized linear mixed modeling will account for correlated observations by including random effects (eg, random intercepts or slopes for participant ID in longitudinal analyses of adherence over time). Survival analysis (ie, Kaplan-Meier estimation; Cox proportional hazards regression) will evaluate PrEP retention. Additional analyses will evaluate descriptive statistics about the enrollment rate, study retention, session attendance, and participant satisfaction. Analyses will be performed in R (R Foundation for Statistical Computing) [77]. Statistical significance will be measured at an α of <.05 for all a priori hypothesis tests. Hypothesis 3a: (primary outcome) compared with standard treatment, the intervention will result in a greater proportion of participants who fill their first PrEP prescription. Hypothesis 3b: compared to standard treatment, the intervention will result in greater adherence to PrEP in those who filled their prescriptions (self-report and laboratory verified urine tenofovir concentrations). Hypothesis 3c: the intervention will be feasible and acceptable by women as demonstrated by enrollment rate, study retention, session attendance, and participant satisfaction scores.

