#### In-Clinic PrEP Screening

After completion of the four motivational sessions, the participant will be scheduled for their initial visit with the nurse practitioner in the CNRA, who will conduct a clinical assessment which will include fourth-generation HIV screening (ie, tests that detect both HIV antibodies and p24 antigens), screening for sexually transmitted infections, a basic metabolic panel to include serum creatinine, and hepatitis B and C screening. The nurse practitioner will review laboratory results. If there is no contraindication for PrEP, the participant will be provided a prescription for PrEP. The decision to prescribe daily oral PrEP or long-acting injectable (LAI) PrEP will be based on a collaborative decision-making process between the patient and nurse practitioner, considering clinical appropriateness, patient choice, and medication availability. Participants on daily oral PrEP will be instructed to take the medication daily and to follow up for laboratory tests in 12 weeks while participating in the intervention. Participants enrolled in LAI-PrEP will be provided with a prescription for a 4-week supply of oral cabotegravir per local clinic protocol of prescribing lead-in medication to monitor side effects before initiating LAI-PrEP. Participants are then instructed to follow up with the nurse practitioner in 4 weeks for their first injection while participating in the intervention. All participants who receive a PrEP prescription from the on-site nurse practitioner will meet with the risk reduction specialist, who will assist those without prescription insurance with enrollment for an appropriate patient assistance program to access medication free of charge through the Advancing Access Program or the Health and Human Services ready, set, PrEP program.

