**Initial efficacy (aim 3)**							
	PrEP eligibility	HIV screening, viral hepatitis screening, pregnancy screening, screening for sexually transmitted diseases, and behavioral risk factors		4, 16, 4		Laboratory results Nurse interview	
	PrEP uptake (primary outcome)	PrEP prescription filled and self-reported initial dose of PrEP taken		10, 16		Self-report	
	PrEP adherence (behavioral)	Video-confirmed dose (intervention, daily oral PrEP) Video-confirmed dose (intervention, long-acting injectable [LAI] PrEP, and initial oral cabotegravir) Follow-up injection (intervention LAI) Self-reported dose daily oral PrEP (intervention and standard treatment)		5-16 n/a and 5-16		Scene health reports, study records, study records, and weekly online survey	
	PrEP adherence (laboratory-confirmed)	Tenofovir concentrations (>1000 ng/mL)		16		Laboratory results	

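### Both between-arm adherence models rest on urine tenofovir alone, although injectable PrEP is allowed in both arms and its own adherence measure enters no named model

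*Protocol article*

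**What the plan says.** **Statistical Analysis.** The article states that "generalized linear modeling will evaluate 2 secondary outcomes as a function of intervention group". The first outcome is "dichotomous verification of adherence based on urine TFV levels >1000 ng/mL (no vs yes". The second is a three-level scale, with "detectable levels of TFV but <1000 ng/mL indicating low adherence and undetectable levels of TFV suggesting nonadherence". Neither is restricted by product. Hypothesis 3b predicts "greater adherence to PrEP in those who filled their prescriptions (self-report and laboratory verified urine tenofovir concentrations", again with no oral-only limit.

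**Table 1, Initial efficacy.** The laboratory adherence row reads "Tenofovir concentrations (>1000 ng/mL", at week 16, with no product limit.

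**In-Clinic PrEP Screening and Control Arm.** In the intervention arm, "The decision to prescribe daily oral PrEP or long-acting injectable (LAI) PrEP will be based on a collaborative decision-making process". The injectable route starts with tablets: "Participants enrolled in LAI-PrEP will be provided with a prescription for a 4-week supply of oral cabotegravir", with the first injection due at four weeks. In the control arm, the partner agency may prescribe either product under its own procedures.

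**Secondary Outcome.** The TFV cut-off is interpreted as a sign of oral PrEP use over the preceding three days, and the urine test is planned in both groups 12 weeks after PrEP is started. Injectables get a separate rule: "Medication adherence for long-acting injectable PrEP will be determined by examining medical records for the timing of the dose".

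**The concern.** The Secondary Outcome section recognises two products and gives each its own adherence measure. Statistical Analysis carries only one of those measures into the arm comparison. A woman on injections at the 12-week or week 16 sample, with every dose on time, would be scored no in the first model and placed in the lowest category of the second. In the intervention arm she will have been prescribed the oral lead-in; once she fills it she is in the Hypothesis 3b population.

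What is at stake is the laboratory-verified part of Hypothesis 3b. Product is chosen after randomisation, and by a different process in each arm: shared choice with the clinic's nurse practitioner in one, the agency's usual practice in the other. If the product mix differs, part of the apparent adherence difference is a difference in mix. If it does not, a real effect is still diluted.

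**Working it through.** The article gives no adherence rate, injectable share, effect size or power, so there is no design figure to reproduce. The check has two parts.

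**1. Which measure reaches which analysis**

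| Measure | Applies to | Named in a between-arm model? |
|---|---|---|
| Urine TFV | Read as oral PrEP use (Secondary Outcome) | Yes, both models |
| Self-reported dosing | Daily oral PrEP, both arms (Table 1) | In Hypothesis 3b, for oral users |
| Dose timing in medical records | Injectable PrEP (Secondary Outcome) | No |
| Follow-up injection | Intervention arm only (Table 1) | No |

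On timing, the lead-in lasts 4 weeks, so a woman on schedule is on injections 12 weeks after starting. At the fixed week 16 sample she would still be on lead-in tablets only if she had started them after about week 12 (16 − 4 = 12).

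**2. Size under the literal coding**

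Inputs from the article: 60 women, two arms, α = .05. Assumed: two-sided tests; 15, 20 or 30 fillers per arm (30 is everyone under 1:1 allocation, a ratio the article does not state); true adherence *a*, the same for oral and injectable users within an arm; injectable share *L*; no tenofovir in the urine of cabotegravir users.

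Apparent rate in an arm = *a* × (1 − *L*).

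Equal true adherence, *a* = 0.70 in both arms:

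| *L*, intervention vs control | Apparent rates | Difference | Rejection rate, chi-square, 15 / 20 / 30 fillers per arm |
|---|---|---|---|
| 20% vs 20% | 0.70 × 0.80 = 0.56 in both | 0 | 0.047 / 0.045 / 0.051 |
| 40% vs 40% | 0.70 × 0.60 = 0.42 in both | 0 | 0.048 / 0.046 / 0.050 |
| 30% vs 10% | 0.70 × 0.70 = 0.49 vs 0.70 × 0.90 = 0.63 | −0.14 | 0.11 / 0.13 / 0.20 |
| 40% vs 10% | 0.70 × 0.60 = 0.42 vs 0.63 | −0.21 | 0.20 / 0.24 / 0.38 |
| 10% vs 40% | 0.63 vs 0.42 | +0.21 | 0.20 / 0.24 / 0.38 |

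Rejection rates are by exact binomial enumeration of the pooled two-sided test. Fisher's exact test gives 0.11 / 0.16 / 0.28 for 40% vs 10%.

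True effect, *a* = 0.80 vs 0.40, 30 fillers per arm:

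| *L*, intervention vs control | Apparent rates | Difference | Power |
|---|---|---|---|
| 0% vs 0% | 0.80 vs 0.40 | 0.40 | 0.91 |
| 20% vs 20% | 0.64 vs 0.32 | 0.32 | 0.72 |
| 40% vs 40% | 0.48 vs 0.24 | 0.24 | 0.49 |
| 40% vs 10% | 0.48 vs 0.36 | 0.12 | 0.16 |

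A smaller true benefit can change sign. For 80% vs 65% with shares of 30% vs 10%, 0.80 × 0.70 = 0.560 against 0.65 × 0.90 = 0.585, so +15 points becomes −2.5.

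If injectable users are scored by dose-timing records, the apparent rate at *a* = 0.70 is 0.70 in both arms, and chi-square rejects at 0.053 (20 per arm) and 0.049 (30 per arm).

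**The case against.** The strongest reply is that TFV was never meant for injectable users. The Secondary Outcome section speaks of daily adherence, ties the cut-off to oral PrEP and gives injectables their own measure; Table 1 also splits behavioural adherence by product. On that reading nobody is miscoded, and the analysis set is a detail for the analysis plan. The reading is plausible, but it does not clear the article. It conflicts with a Hypothesis 3b population defined by filling a prescription. It compares only women who chose tablets, a choice made after randomisation. And it leaves injectable users out of every stated arm comparison of adherence. Statistical Analysis also mentions longitudinal adherence models and a survival analysis of retention, but does not say how injectable use enters either.

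Three stronger inferences are tempting and not supported:

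- A reader might infer that every woman on cabotegravir is coded nonadherent. No sentence says so; it is what a literal application of the two models gives.
- A reader might infer that women on the oral lead-in are generally caught as well. The 4-week lead-in would normally be over at sampling, so this happens only after a late start.
- A reader might infer that the arm comparison necessarily follows product choice. A false difference needs unequal injectable shares, and the documents give no share for either arm.

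It is also fair to say that this is a secondary outcome in a 60-woman pilot, and that the limitations section concedes follow-up is too short for conclusions about adherence.

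**Conclusion.** The point holds in conditional form. Secondary Outcome and Statistical Analysis are not reconciled: the between-arm models are TFV-only with no product limit, and the injectable measure enters none of them. Applied as written, an adherent woman on injections is scored as a failure. With unequal injectable shares the comparison is biased in either direction (±21 points at 40% and 10%, with true adherence of 70% in both arms). With equal shares there is no false difference and the test keeps its level, but a true effect is attenuated and power is lost.

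The shares, adherence rates and filler counts are assumptions. That cabotegravir yields no urinary tenofovir is general pharmacology that the article does not state, though its separate measure for injectables is consistent with it. The primary outcome, PrEP uptake, is unaffected.

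**What to change.** - In Statistical Analysis and the laboratory row of Table 1, define one product-specific binary outcome for the Hypothesis 3b arm comparison, used in both arms. For women on tenofovir-based oral PrEP it is urine TFV >1000 ng/mL; for women on injectable PrEP it is the dose-timing record already named under Secondary Outcome. Fit the between-arm model to this outcome.
- Show the results by product as well.
- Limit the three-level TFV analysis to women on a tenofovir-based product at sampling, and label it descriptive.
- Record the current product at the adherence assessment in both arms.

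**Cost.** No treatment changes, but more than wording is needed. The Control Arm section lists only appointment attendance and whether a prescription was given as data returned by the partner agency; current product and injection dates must be added, with participant consent. Two limits remain. The outcome mixes a laboratory test with a record-based measure, so some sensitivity to product mix can persist. And restricting to women who filled a prescription, as Hypothesis 3b does, is itself a post-randomisation selection and should be reported as such.

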#### Monetary Incentives

Participants will receive monetary incentives for completing project-related tasks and engaging in desirable health-promoting behaviors. Each participant will receive US $25 for the baseline data collection, US $10 per session for attending 4 weekly motivational counseling sessions, US $25 for the initial nurse visit with laboratory tests, US $10 for providing proof of the initial prescription fill, US $1/day for uploading daily adherence videos during weeks 5-16 (those on LAI-PrEP will receive US $1/day for weeks 4-8 and US $60 for proof of injection for weeks 9-16), US $25 each for data collection at 4-weeks and 1-weeks post baseline, US $25 for the 90-day follow-up visit with the nurse practitioner, and US $50 for completing the follow-up data collection at week 16 (US $309 possible for the entire intervention).

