#### Control Arm

Participants randomized to the control arm will receive standard of care PrEP information along with a referral and a scheduled appointment with Allies in Hope. Transportation assistance for appointment attendance will be provided. In this agency, if there is no contraindication for PrEP, the participant will be provided a prescription for daily oral PrEP or long-acting injectable PrEP and follow up with the community-based partner per normal procedures at that facility. Allies in Hope will provide the research team with information regarding appointment attendance and whether a prescription was provided to the participant, with consent from the participant. Participants in standard treatment will continue to receive their regular SUD treatment services.

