#### Monetary Incentives

Participants in the control arm will receive the same incentives, except for the weekly session amounts, for a possible total of US $269 for the entire study. Standard treatment participants will not have access to the Scene Health app and will be asked to respond to a daily yes or no question regarding medication adherence through REDCap (Research Electronic Data Capture; Vanderbilt University) with the same US $1/response incentive.

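### Daily dose reporting is set for study weeks 5-16 in both arms, which fits the intervention arm's start of PrEP but can miss up to 28 days of early use in the control arm

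*Protocol article*

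**What the plan says.** All references are to the Protocol article.

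- **Retention analysis (Statistical Analysis).** "Survival analysis (ie, Kaplan-Meier estimation; Cox proportional hazards regression) will evaluate PrEP retention". Hypothesis 3b in the same section compares adherence, by self-report and by urine tenofovir, among women who filled their prescriptions.
- **Window for dose reports (Table 1, Initial efficacy).** The behavioral adherence row includes "Self-reported dose daily oral PrEP (intervention and standard treatment") and gives weeks 5-16.
- **Payments (Monetary Incentives, both arms).** Intervention women receive "US $1/day for uploading daily adherence videos during weeks 5-16", with "US $309 possible for the entire intervention". Control women "will be asked to respond to a daily yes or no question regarding medication adherence through REDCap", on the same incentives less the session payments, "for a possible total of US $269 for the entire study".
- **Access to the prescriber.** Intervention arm: "After completion of the four motivational sessions, the participant will be scheduled for their initial visit with the nurse practitioner". Control arm: standard PrEP information "along with a referral and a scheduled appointment with Allies in Hope". No appointment date or waiting period is given for controls.
- **A different anchor.** Medication Adherence Monitoring counts the 12 weeks of video uploads from the start of PrEP. Secondary Outcome places the urine tenofovir measurement 12 weeks after initiation in both groups, whereas Table 1 places it at week 16.

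**The concern.** A window fixed in study weeks captures use from about the first dose only if women start at about week 4. That holds by design in the intervention arm. In the control arm nothing holds the start back, so part of a woman's early use can fall before the first scheduled dose report.

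Two comparisons are affected. Self-reported adherence under Hypothesis 3b would set early use in one arm against somewhat later use in the other. In the retention analysis, stops in the first weeks would be dated to the day in the intervention arm but only bracketed in the control arm. An analysis plan can choose a time origin and censoring rule, but it cannot recover daily answers that were never requested. The collection window therefore matters now.

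The point concerns daily oral PrEP. Timing of injections is taken from medical records.

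**Working it through.** **1. Reproduce the incentive totals (daily oral schedule).** Baseline 25; four sessions 4 x 10 = 40; nurse visit 25; proof of fill 10; daily uploads 12 weeks x 7 x 1 = 84; two interim data collections 2 x 25 = 50; 90-day visit 25; week-16 data collection 50.

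25 + 40 + 25 + 10 + 84 + 50 + 25 + 50 = **309**, as stated. Control: 309 - 40 = **269**, as stated.

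The control total therefore funds 84 daily responses. Responses throughout 16 weeks would be 112 days and 269 - 84 + 112 = US $297. The total alone fixes the number of days. The calendar placement comes from Table 1 and from the weeks 5-16 in the incentive schedule that the control arm shares.

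**2. Length of the gap.** Weeks 5-16 are 12 weeks, so week 5 opens on day 28. A woman who starts s weeks after baseline has 4 - s weeks on drug before it opens: 28, 21, 14, 7 or 0 days for s = 0, 1, 2, 3, 4.

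**3. Share of control starters who stop inside the gap.** The formula is 1 - (1 - h)^(4 - s), where h is the weekly stopping probability. The documents give no stopping rate, so h is assumed.

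| Start (weeks after baseline) | h = 2% | h = 5% | h = 10% |
|---|---|---|---|
| 0 | 7.8% | 18.5% | 34.4% |
| 1 | 5.9% | 14.3% | 27.1% |
| 2 | 4.0% | 9.8% | 19.0% |
| 3 | 2.0% | 5.0% | 10.0% |
| 4 | 0% | 0% | 0% |

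**4. Effect on a Cox comparison.** This was simulated with 4,000 women per arm and a true hazard ratio (intervention versus control) of 1. Assumptions: control starts uniform over weeks 0-4, intervention starts uniform over weeks 4-6, Weibull stopping times, and follow-up to week 16.

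| Stopping pattern | Stopped by 12 weeks | Controls stopping in gap | Complete data | Dropped, clock from first dose | Delayed entry at week 5 | Kept as event at week 5 |
|---|---|---|---|---|---|---|
| Constant hazard | 30% | 6.0% | 0.97 | 1.21 | 0.97 | 0.97 |
| Constant hazard | 50% | 10.5% | 0.99 | 1.24 | 0.99 | 1.00 |
| Front-loaded (shape 0.6) | 30% | 10.5% | 0.98 | 1.51 | 0.96 | 1.01 |
| Front-loaded (shape 0.6) | 50% | 19.1% | 1.02 | 1.62 | 1.00 | 1.08 |

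The complete-data column shows the simulation noise. The bias comes from dropping early stoppers. Keeping them, even with a coarse stop time, removes nearly all of it.

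**5. The competing anchor.** For a control woman who starts at baseline, 12 weeks after initiation is week 12, while Table 1 samples urine at week 16. The two rules can differ by up to four weeks in the control arm. They roughly coincide for an intervention woman who starts at week 4.

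**The case against.** The strongest reply is that the documents do not settle on the calendar window. The control-arm text gives no start week for the daily question, 84 responses would equally fit 12 weeks from first dose, and two other sections count from initiation. The Table 1 cell is also broken in extraction. This stands in part: the passages conflict. But the initiation-anchored video rule applies to the intervention arm only, and the urine measure is a single sample that cannot date a stop. Neither provides control dose reports before week 5.

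A reader might infer that early control stoppers are never recorded, so that retention is left-truncated in one arm. The documents do not support that. The primary outcome records the fill and first dose by self-report at weeks 10 and 16. Pharmacy and medical records are listed as efficacy sources, and the referral agency reports attendance and prescription. All randomized women are followed from baseline. An early stopper stays in the sample, and her answers from week 5 would show that she is off drug, so her stop time is interval-censored. Truncation arises only if the analyst drops her, which no section says.

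Nor do the documents say that controls start at baseline or that stopping is concentrated in the first weeks. The first is inferred from the absence of a stated wait, and assessment, prescription and fill must come before a dose. The second is an assumption.

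It is also fair that the definition, time origin and censoring rule for retention may sit in an analysis plan that is not shown. Their absence is no part of this point.

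**Conclusion.** The mismatch holds in a limited form. As Table 1 and the incentive schedule stand, a control woman who starts daily oral PrEP before week 5 has up to 28 days of use with no scheduled dose record. The intervention arm has no matching gap. An early control stop can be placed only between first dose and week 5, and adherence and retention would be compared over different stretches of use.

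The size of any bias cannot be fixed from the documents. There is no gap if controls start at week 4 or later. Under the assumed rates the hazard ratio stays near 1 (0.97-1.08) if early stoppers are kept as events at week 5. It moves against the intervention (1.21-1.62 when the truth is 1) only if they are dropped and time runs from first dose. The calendar and initiation anchors contradict each other and must be reconciled.

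Priority is low to moderate. Retention is not the primary outcome and is not named in Hypotheses 3a-3c, and the article itself says that follow-up in this pilot is too short for conclusions on adherence.

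**What to change.** 1. **Use one anchor for dose reports.** Start the existing control REDCap question, like the intervention videos, at each woman's first dose and run it for 12 weeks. That is 84 responses, so US $269 and equal incentives are kept. Prompting controls from baseline instead would pay up to 112 responses (US $297), 28 more than the intervention arm, and would add prompting in one arm only.
2. **Reconcile the passages.** Bring Table 1, Monetary Incentives, Medication Adherence Monitoring and Secondary Outcome to the same time base, including the timing of the urine sample.
3. **Measure from first dose.** Compare adherence and retention from the date of first dose in both arms over the same duration. A woman who starts five weeks after baseline completes 12 weeks only at week 17, after the final data collection at week 16. State whether reporting runs on or is censored at week 16.
4. **Keep early stoppers.** Include any woman who stopped before her monitoring began as an event with an interval-censored stop time. Use delayed entry only as a sensitivity analysis.

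The cost is that prompts must be triggered by each woman's reported start rather than a fixed week. The proof of initial fill, which the shared incentive schedule already pays for, could serve as the trigger, with the date of first dose asked at that contact. No extra payment or visit is needed for this. For women already enrolled, the date of first dose and any stop before week 5 can still be asked at the next scheduled survey.

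### Hypothesis 3b tests adherence only among women who filled a prescription, a group that the intervention is meant to enlarge, so the comparison is not protected by randomisation

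*Protocol article*

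**What the plan says.** All of this is in the Methods of the protocol article.

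- **Hypothesis 3b (Statistical Analysis).** The secondary claim is that "compared to standard treatment, the intervention will result in greater adherence to PrEP in those who filled their prescriptions", judged by self-report and by urine tenofovir. The same section applies a .05 significance level to every a priori hypothesis test, so 3b reads as a formal test between arms and not as a description.
- **Hypothesis 3a (Statistical Analysis).** The primary claim is that "compared with standard treatment, the intervention will result in a greater proportion of participants who fill their first PrEP prescription".
- **Primary Outcome.** The outcome is "PrEP uptake defined as filling the PrEP prescription and taking at least 1 dose of the medication by 2 weeks following their visit". Filling is therefore one of its two components.
- **Model sentence (Statistical Analysis).** For urine tenofovir, "generalized linear modeling will evaluate 2 secondary outcomes as a function of intervention group". It names no analysis set. The three-level version ends with "undetectable levels of TFV suggesting nonadherence".
- **Timing of tenofovir.** Secondary Outcome has it "detected in urine measured at 12-weeks post-PrEP initiation (both groups"). Table 1 lists it at study week 16.
- **Injectable users (Secondary Outcome).** Their adherence is judged from the timing of doses in medical records, not from tenofovir.

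**The concern.** Randomisation makes the two arms comparable as whole groups. It does not make two subsets comparable when membership depends on something that happened later and that the treatment was built to change.

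The protocol works actively on that membership in one arm. Under Medication Adherence Monitoring, intervention women who have not filled within two weeks are brought back to the nurse practitioner to discuss their concerns. Under Motivational Messaging, intervention women who have not chosen to start PrEP, and who agree, keep receiving messages. Control women follow the partner agency's normal procedures. If the intervention works, its fillers will include women who would not have filled under referral, and the control fillers will not include their counterparts.

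If those extra women take PrEP less reliably, a useful programme can appear to lower adherence. If they take it more reliably, the effect on adherence is overstated. Either result could misdirect the larger trial that the Limitation and Strengths section foresees.

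**Working it through.** The article states no uptake rate, adherence rate, effect size or power, so there is no figure of its own to reproduce. The check asks how far the filler-only contrast can move under assumed rates.

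**Inputs.** From the article: 60 women, two arms. Assumed: 1:1 allocation (30 per arm; the ratio is not stated) and every rate below. Also assumed: no woman fills under control who would not fill under the intervention.

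**Notation**
- u0, u1: proportion filling in the control and intervention arms
- a0, a1: adherence, under control and under intervention, of women who would fill in either arm
- aI: adherence of women who fill only because of the intervention

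**Formulas**
- Among fillers: control = a0; intervention = [u0·a1 + (u1 − u0)·aI] / u1.
- Among all randomised, non-fillers counted as not adherent: control = u0·a0; intervention = u0·a1 + (u1 − u0)·aI.
- Rearranged, the filler-only difference = (a1 − a0) + [(u1 − u0)/u1]·(aI − a1). The second term is the selection bias relative to women who would fill anyway. It takes the sign of aI − a1 and vanishes only if u1 = u0 or aI = a1.

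**One case in full** (u0 = 20%, u1 = 50%, a0 = a1 = 70%, aI = 40%)
- Intervention fillers: (0.20 × 0.70 + 0.30 × 0.40)/0.50 = 0.26/0.50 = 52%, against 70% in control fillers: −18 points.
- All randomised: 0.20 × 0.70 = 14% against 0.26 = 26%: +12 points.
- Expected fillers at 30 per arm: 30 × 0.20 = 6 and 30 × 0.50 = 15.

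**Other cases** (control v intervention)

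| u0/u1 | a0/a1 | aI | Fillers | Difference | All randomised | Difference |
|---|---|---|---|---|---|---|
| 20/60 | 70/70 | 30 | 70 v 43 | −27 | 14 v 26 | +12 |
| 30/60 | 70/80 | 30 | 70 v 55 | −15 | 21 v 33 | +12 |
| 30/60 | 70/80 | 50 | 70 v 65 | −5 | 21 v 39 | +18 |
| 30/60 | 70/80 | 70 | 70 v 75 | +5 | 21 v 45 | +24 |
| 30/60 | 70/80 | 90 | 70 v 85 | +15 | 21 v 51 | +30 |
| 20/60 | 70/80 | 90 | 70 v 87 | +17 | 14 v 52 | +38 |

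The full grid used uptake pairs 20/40, 30/60, 20/60, 40/60 and 40/80%, a0 = 70%, a1 = 70 or 80%, and aI = 30, 50, 70 or 90%. The filler-only difference ran from −27 to +17 points and the all-randomised difference from +6 to +40. The latter is positive throughout because every scenario raises uptake and none lowers adherence in women who would fill anyway.

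**Where the sign turns.** With a true benefit of 10 points in women who would fill anyway (70% to 80%), the filler-only difference is negative when aI < (0.7·u1 − 0.8·u0)/(u1 − u0). At 30/60 this is (0.42 − 0.24)/0.30 = 60%. It is 50% at 40/60 and 65% at 20/60.

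**Simulated trials** (30 per arm, uptake 30/60, a0/a1 = 70/80, 20,000 runs). For aI = 30, 50 and 70%, the filler-only estimate is negative in 77%, 60% and 39% of trials; the all-randomised estimate is negative in 11%, 5% and 1%. In the 70% case the expected filler-only difference is +5, so its negative results are chance in small groups (about 9 v 18 fillers) and not a reversed expectation.

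**Timing.** Twelve weeks after initiation falls at week 16 only for a woman who starts in week 4; a start in week 6 gives week 18. The two stated timings are therefore not the same measurement.

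**The case against.** **The model is not restricted to fillers.** The generalised linear model sentence is silent on the analysis set, and the undetectable category could hold women who never started. This stands as far as it goes: the restriction sits in the hypothesis wording, and one cannot say that every adherence analysis is confined to fillers. But nothing in the article counts never-starters as nonadherent or adds an adherence comparison over all randomised women. If all women were meant, 3b is worded wrongly and needs the same edit.

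**Never-starters can be sampled.** From the Secondary Outcome section a reader might infer that women who never start have no sampling date. Table 1's week 16 entry does not support that; it offers a fixed visit. The real defect is that two timings stand side by side.

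**Retention.** A reader might infer that the same restriction governs the plan that "Survival analysis (ie, Kaplan-Meier estimation; Cox proportional hazards regression) will evaluate PrEP retention". That sentence gives no population, time origin or hypothesis between arms, and such detail may properly sit in an analysis plan not shown here. No finding is made on it.

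**The size is assumed.** Correct. Reversal requires that women induced to fill adhere sufficiently less well than the others. If they adhere equally well, there is no selection bias; if better, it favours the intervention. A reader might conclude that the sign will reverse or that 3b is uninterpretable; the documents support neither.

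**The remedy answers a different question.** Also correct. Counting never-starters as nonadherent mixes uptake with adherence. In the case worked in full, +12 points appears although adherence is unchanged in women who would fill anyway.

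**It is a pilot.** Limitation and Strengths already says that follow-up is too short for conclusions on adherence. That lowers the reliance placed on 3b, but for another reason; it does not mention this selection.

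**Conclusion.** The point holds for Hypothesis 3b as worded. It sets a formal between-arm test in a subgroup defined after randomisation by an event that Hypothesis 3a expects the intervention to change. The non-comparability follows from the text; its size and direction do not. Whether the bias is large, small, favourable or unfavourable rests on assumed uptake and on how women drawn in by the intervention behave, neither of which the article gives.

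It should be fixed, but it is not critical: 3b is a secondary hypothesis in a pilot, and the comparison of uptake in Hypothesis 3a is untouched.

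**What to change.** - Reword 3b so that the tested comparison is the proportion adherent to PrEP at week 16 among all 60 women, in the arm to which they were randomised, with never-starters counted as not adherent.
- Classify oral users by urine tenofovir and long-acting injectable users by the injection timing in medical records.
- State this analysis set in the model sentence, and give one tenofovir timing for the tested outcome in both Table 1 and Secondary Outcome.
- Report adherence among fillers, including self-report, by arm as description, with no efficacy claim.

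**Cost.** The change is mainly one of wording and should be settled before any comparison by arm is seen. Table 1 already schedules tenofovir at week 16, and never-starters need no sample. One practical check: the Control Arm section says that the partner agency will share appointment attendance and whether a prescription was given, but does not mention injection dates, so access to those for control women should be confirmed.

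The adherence percentages will be lower, because never-starters enter the denominator. The outcome will combine uptake with adherence, so it overlaps the primary outcome and does not isolate the effect of adherence support. The report should say so.
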